## Abstract

**Background:**

Non-invasive ventilation (NIV) is indicated to avoid orotracheal intubation (OTI) to reduce hospital stay and mortality. Patients infected by SARS-CoV2 can progress to respiratory failure (RF); however, in the initial phase, they can be submitted to oxygen therapy and NIV. Such resources can produce aerosol and can cause a high risk of contagion to health professionals. Safe NIV strategies are sought, and therefore, the authors adapted diving masks to be used as NIV masks (called an Owner mask).

**Objective:**

To assess the Owner mask safety and effectiveness regarding conventional orofacial mask for patients in respiratory failure with and without confirmation or suspicion of COVID-19.

**Methods:**

A Brazilian multicentric study to assess patients admitted to the intensive care unit regarding their clinical, sociodemographic and anthropometric data. The primary outcome will be the rate of tracheal intubation, and secondary outcomes will include in-hospital mortality, the difference in PaO_2_/FiO_2_ ratio and PaCO_2_ levels, time in the intensive care unit and hospitalization time, adverse effects, degree of comfort and level of satisfaction of the mask use, success rate of NIV (not progressing to OTI), and behavior of the ventilatory variables obtained in NIV with an Owner mask and with a conventional face mask. Patients with COVID-19 and clinical signs indicative of RF will be submitted to NIV with an Owner mask [NIV Owner COVID Group (*n* = 63)] or with a conventional orofacial mask [NIV orofacial COVID Group (*n* = 63)], and those patients in RF due to causes not related to COVID-19 will be allocated into the NIV Owner Non-COVID Group (*n* = 97) or to the NIV Orofacial Non-COVID Group (*n* = 97) in a randomized way, which will total 383 patients, admitting 20% for loss to follow-up.

**Discussion:**

This is the first randomized and controlled trial during the COVID-19 pandemic about the safety and effectiveness of the Owner mask compared to the conventional orofacial mask. Experimental studies have shown that the Owner mask enables adequate sealing on the patient’s face and the present study is relevant as it aims to minimize the aerosolization of the virus in the environment and improve the safety of health professionals.

**Trial registration:**

Brazilian Registry of Clinical Trials (ReBEC): RBR – 7xmbgsz. Registered on 15 April 2021.

## Administrative information

Note: the numbers in curly brackets in this protocol refer to SPIRIT checklist item numbers. The order of the items has been modified to group similar items (see http://www.equator-network.org/reporting-guidelines/spirit-2013-statement-defining-standard-protocol-items-for-clinical-trials/).

## Introduction

### Background and rationale {6a}

After the emergence of a new coronavirus called SARS-CoV-2, the COVID-19 disease was initially characterized by fever, sore throat, cough and dyspnea, and mainly by manifestations of the respiratory system [1]. Other manifestations, including neurological and micro-hemodynamic findings, were added to its clinical spectrum during the course of the COVID-19 pandemic [2], with 81% of patients having mild symptoms, 14% being severe, and 5% being very severe [3, 4].

Non-invasive ventilation (NIV) traditionally has the indication of avoiding orotracheal intubation (OTI), reducing hospital stay and mortality, being an important resource in the intensive care repertoire [5]. Westhoff et al. [6] showed that NIV was associated with elevated mortality when the ratio of the partial pressure of oxygen in arterial blood (PaO_2_) to the inspired oxygen fraction (FiO_2_) (PaO_2_/FIO_2_) was < 150 mmHg [7], also demonstrating that delayed intubation is prognostically unfavorable.

It should be noted that the recommendations for NIV for patients with COVID-19 are still under discussion, but what has been shown so far is that there is generally a good response to oxygen therapy and NIV in COVID-19 due to low VA/Q ratio (Ltype) [8], with low intrapulmonary shunt with consequent severe oxygenation disorder as in the traditional acute respiratory distress syndrome to accurately indicate OTI.

It is recommended to institute NIV in addition to oxygen supplementation when there is worsening of respiratory discomfort, while OTI and the institution of mechanical ventilation becomes a priority in case of failure in this therapy. It is estimated that 30.8% of people infected with SARS-CoV2 remain asymptomatic, and 15 to 20% among those who are symptomatic require hospitalization, of which 5% progress to a critical condition—a condition which requires more complex interventions [3, 4].

Although the significant escape of infectious aerosols is a risk in NIV, it is recommended that aerosolization is minimized by the use of an appropriate interface and the use of filters such as the high-efficiency particulate arrestance (HEPA) in the expiratory branch [9, 10]. It is additionally recommended that all non-invasive treatments should be monitored closely due to the risk of rapid clinical deterioration [6]. According to Landry et al. [11], mask leaking from positive pressure systems may be a major source of environmental contamination and nosocomial spread of infectious respiratory diseases and that improvised diving masks show greater leaking at higher flow rates compared to standard continuous positive airway pressure (CPAP) masks at pressures greater than 10–12 cmH_2_O. Therefore, NIV should be used with CPAP pressure levels of up to 12 cmH_2_O, with the aim of minimizing aerosolization, maintaining peripheral oxygen saturation (SpO_2_) between 93 and ≤ 96%, inspired fraction of oxygen (FiO_2_) ≤ 50% and respiratory rate (RR) < 24 bpm, which should be evaluated within 1 h [11, 12].

Predicting the lack of materials to meet the needs of these patients in the intensive care units (ICU), the “Mergulhadores do Bem” group from the Universidade de Santa Cruz do Sul—RS/Brazil, inspired by the idea implemented in Italy and used in hospitals (https://www.isinnova.it/easy-covid19/), adapted masks used for diving (snorkeling) to be used as NIV masks, called the Owner mask, which can be adapted to traditional mechanical ventilators and portable non-invasive ones (http: //www.mergulhadoresdobem.com.br/).

Thus, in view of the urgent need to develop measures to assist in ventilatory care for patients with SARS-CoV-2 infection, the Owner mask was designed to prioritize protection and assist in respiratory function, allowing an adequate seal on the patient’s face and minimizing the virus aerosolization in the environment. Considering that patients with COVID-19 can benefit from early non-invasive ventilatory strategy and that the interface for NIV needs to avoid aerosolization for the environment to reverse/minimize the acute respiratory failure (RF), the present study aims to assess the safety and efficacy of the Owner mask in relation to the conventional orofacial mask for performing NIV.

### Objectives {7}

The primary objective of the study is to determine whether the use of Owner mask is effective in reducing the risk of OTI compared to conventional orofacial mask for patients with and without COVID-19 requiring NIV and the secondary objectives were to determine safety and effectiveness by comparing physiological measurements, mortality, length of stay measures, adverse effects, and patient satisfaction.

### Trial design {8}

This is a three-phase, parallel group, randomized, non-blinded, controlled, multicentric study guided by outcome. The allocation ratio is 1:1 in favor of the Owner mask to maximize learning about the experimental treatment, while also allowing a wider pool of patients to have access to the experimental treatment in order to support recruitment.

## Methods: participants, interventions, and outcomes

### Study setting {9}

The setting involved the following Brazilian hospitals: Hospital Santa Cruz (HSC) of Universidade de Santa Cruz do Sul, Hospital Geral Otávio de Freitas (HGOF), and Hospital Regional do Agreste—Universidade Federal de Pernambuco.

### Eligibility criteria {10}

The inclusion criteria are as follows: age ≥ 18 years at time of signing of informed consent form, patients with or without SARS-CoV-2 suspicious or confirmation of both genders, clinical indication to implement NIV, chronic obstructive pulmonary disease exacerbation with hypercapnic acute respiratory failure, congestive heart failure (NYHA 4), hospitalized with SpO_2_ ≤ 94% on room air or PaO_2_/FiO_2_ ≤ 300 mmHg, willingness of study participant to accept randomization to any assigned treatment arm, and must agree to not enroll in any other study of an antiviral agent prior to completing the 28-day follow-up.

### Exclusion criteria

The exclusion criteria are as follows: comatose patients (Glasgow Coma Scale < 8) or unable to protect the airways; patients who refuse to receive NIV; presence of facial anomalies, facial trauma or facial burn; severe hematemesis or massive hemoptysis; hemodynamically unstable patients (systolic blood pressure (SBP) < 80 mmHg) or receiving vasopressors/inotropes: ongoing angina/acute myocardial infarction or recently developed arrhythmia with hemodynamic impact; patients who underwent esophageal or recent upper respiratory tract surgery (≤ 2 weeks); cardiorespiratory arrest; and patients or legal guardian who do not sign the informed consent form.

### Who will take informed consent? {26a}

Informed consent will be obtained from eligible patients or their substitute decision-makers (for patients lacking decision-making capacity) by study physicians and physiotherapists or other trial staff with delegated responsibility.

### Additional consent provisions for collection and use of participant data and biological specimens {26b}

Not applicable.

### Interventions

#### Explanation for the choice of comparators {6b}

The active arm is the use of the Owner mask to implement NIV, in addition to routine supportive care. The Owner mask (Owntec Soluções em Engenharia, Santa Cruz do Sul, Brazil) was chosen for evaluation because there is safety data from the pilot study which proved reduced air leakage due to its better seal on the patient’s face. The control arm is composed of patients who will undergo NIV using the traditionally used orofacial interface.

#### Intervention description {11a}

Patients admitted to the emergency or ICU will be screened and recruited using a convenience sample (Fig. 1). Those with suspicion or confirmation of COVID-19, with clinical signs indicative of respiratory insufficiency, will be submitted to NIV with Owner mask (Group NIV Owner COVID) or with conventional orofacial mask (Group NIV orofacial COVID), and those patients in RF due to causes not related to COVID-19 will be allocated into the NIV Owner Group or to the orofacial NIV Group in a randomized way.

**Fig. 1 Fig1:**
[figure not shown]
Flowchart of the study

NIV will be instituted in CPAP or bi-level positive airway pressure (BiPAP) mode with expiratory positive airway pressure (EPAP) and inspiratory positive airway pressure (IPAP) levels of up to 10–12 cmH_2_O. NIV will be used for 30 min to 1 h for patients with COVID-19, with gas analysis before and after this period. Sessions in non-COVID-19 patients can last up to 2 h, and NIV can be used intermittently, as long as there is no clinical worsening or signs of failure [13, 14].
CPAP: hypoxemic respiratory failure, with positive expiratory end pressure (PEEP) between 5 and 12 cmH_2_O and FiO_2_ minimum to maintain SpO_2_ ≥ 94%BIPAP: hypercapnic respiratory failure, start with IPAP necessary to maintain SpO_2_ > 94% and with maximum levels up to 10–12 cmH_2_O. Tidal volume up to a maximum of 9 ml/Kg/predicted weight, EPAP (PEEP) between 6 and 8 cmH_2_O and FiO_2_ minimum enough for SpO_2_ ≥ 94%

NIV will be performed by a conventional mechanical ventilator, preferably by SERVO-S (Maquet Critical Care, São Paulo, Brazil), or by the one available at each research center. The criteria for its interruption will be those of clinical worsening (determined by the medical team) such as the occurrence of hemodynamic instability, depression of the cognitive state, psychomotor agitation, lack of airway defense, lack of adaptation to the interface, and severe bronchospasm [15]. Success or reduction in the severity of RF will be considered by the oxygenation index through the PaO_2_/FiO_2_ > 200, reduction in RR < 30 bpm and SpO_2_ ≥ 94% [12, 16].
NIV Owner group (experimental group)
Patients with suspected or confirmed COVID-19 undergoing NIV with an Owner maskPatients with RF due to causes unrelated to COVID-19 submitted to NIV with Owner maskNIV orofacial group (control group)
Patients with suspected or confirmed COVID-19 undergoing NIV with conventional orofacial maskPatients with RF due to causes unrelated to COVID-19 submitted to NIV with conventional orofacial mask

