#### Secondary outcome measure

In-hospital mortality [period: up to 30 days]Differences in the PaO_2_/FiO_2_ ratio regarding the baseline values (before NIV) [period: 48 h]Improvement in the PaO_2_/FiO_2_ ratio after beginning NIV [period: 1 h after NIV]PaCO_2_ levels [period: 1 to 12 h after NIV]Blood pressure (BP) and hypotension incidence (SBP < 80 mmHg or mean arterial pressure < 60 mmHg) [period: up to 2 h after NIV]Time between beginning NIV and its endICU time [time period: up to 30 days]Length of hospital stay of patients who used NIVAdverse events of the mask [period: obtained at pre-hospital discharge]Comfort of the patient with the mask (visual analog scale—VAS) [period: obtained at pre-hospital discharge]Satisfaction level (PGIC) after using NIV [period: obtained at pre-hospital discharge]NIV success rate with masks [deadline: 1 h since the beginning of NIV]Tidal volume (Vt), minute volume (MV), peak pressure (Ppeak), respiratory rate (RR), FiO_2_, inspiratory time (Ti), expiratory time (Te), air leak, inspiratory minute volume (VMi), and expiratory minute volume (VMe) obtained in NIV [period: 1 h after NIV]

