#### Implementation {16c}

Patients will receive NIV through the Owner mask or the conventional orofacial mask according to the sequence of the previous randomization sent to each hospital. The choice of the traditional orofacial mask or the Owner mask will occur by randomization performed by a random table generated by a computer program that will determine the patient allocation group and the treatment allocation will be determined by the treating team opening the next sealed envelope. Both groups will be allocated to receive NIV by adapted mask or conventional mask with COVID-19 confirmed, or with other respiratory diseases. The random table will be the same for both groups of patients (with COVID-19 and/or another respiratory disease).

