#### Vital signs and respiratory effort

SpO_2_ will be measured using pulse oximetry (DX2010, Dixtal, Manaus, AM, Brazil), and BP and heart rate (HR) will be assessed through digital monitoring (DX2010, Dixtal, Manaus, AM, Brazil). Hypotension will be considered when SBP < 80 mmHg or mean arterial pressure < 60 mmHg) within 24 h after NIV. RR will be obtained by a plethysmographic signal provided by the VM monitor (SERVO-S, Maquet Critical Care, São Paulo, SP, Brazil). The respiratory effort will be qualified by inspection when the patient develops tachypnea, use of accessory muscles, flapping of the nose, change in breathing pattern, shallow breathing, and abnormal movements of rib cage [25]. Such measures will be performed before and after 1 h of NIV institution.

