#### Ventilatory parameters

The following ventilatory variables will be monitored in the mechanical ventilation: Vt, MV, Ppeak, RR, FiO_2_, Ti, Te, air leak, VMi, and VMe. Such variables will be obtained before and after the application of NIV. Such measures should be carried out after 1 h of NIV adaptation.

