#### Arterial blood gas analysis

Arterial blood gasses will be obtained according to the routines of each center participating in the research. For research purposes, the gasometric variables will be assessed at the baseline (before NIV) and from 1 to 12 h from the beginning of NIV.

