### Statistical methods

#### Statistical methods for primary and secondary outcomes {20a}

The SPSS software program (version 25.0, IBM, Armonk, NY, USA) will be used for data analysis using the Generalized Estimation Equations (GEE) model. The normality of the data will be assessed using the Kolmogorov-Smirnov test. Identity function, unstructured work correlation matrix, and covariance matrix of the robust estimator will be used using the Bonferroni post hoc test when significant. The chi-squared test will be used to compare the proportions of categorical variables studied in the groups and the Mann-Whitney *U* test to compare the distributions of continuous variables between groups (*p* < 0.05). Analysis by intention-to-treat will be performed to include patients who did not allow analysis of outcomes.

The effect size will be estimated according to Cohen [28], who suggested a cutoff value greater than or equal to 0.8 representing a large effect size, between 0.8 and 0.2 as a medium effect size, and values below 0.2 as a small effect size. The same will be calculated using the variation obtained before and after the intervention, as well as for the post-intervention moment between the groups analyzed. The effect size will be calculated using [name] Effect Size Calculator [http://www.uccs.edu/lbecker/].

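### The Mann-Whitney test named for continuous outcomes ignores hospital although the ventilator may differ by hospital, so air leak and the other ventilator-read secondary outcomes may lose power; a hospital-stratified test avoids this at almost no cost

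*Protocol article*

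**What the plan says.** - **Device.** Intervention description {11a} (text after Fig. 1) prefers the SERVO-S for NIV but allows it to be delivered "or by the one available at each research center".
- **Outcomes read from it.** Ventilatory parameters lists "Vt, MV, Ppeak, RR, FiO_2_, Ti, Te, air leak, VMi, and VMe", which is ten variables. The list of secondary outcomes includes them, ending with "air leak, inspiratory minute volume (VMi), and expiratory minute volume (VMe) obtained in NIV", at 1 h.
- **Baseline.** Ventilatory parameters says that these variables are taken before and after NIV is applied.
- **Respiratory rate.** Vital signs and respiratory effort names a single source: "RR will be obtained by a plethysmographic signal provided by the VM monitor (SERVO-S".
- **Allocation.** Sequence generation {16a} uses blocks of 10. Implementation {16c} gives treatment "according to the sequence of the previous randomization sent to each hospital". This implies a separate list per hospital but does not say so. Study setting {9} names three hospitals.
- **Analysis.** Statistical methods {20a} and Methods for additional analyses {20b} both name the Mann-Whitney U "test to compare the distributions of continuous variables between groups". Both also name a GEE model. Section {20a} gives its link, working correlation and variance estimator; neither section mentions a hospital or ventilator term.

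**The concern.** Different ventilators may measure leak, volumes and times differently. If the device differs by hospital, the absolute readings carry a hospital offset that has nothing to do with the mask. A Mann-Whitney test on all readings together ranks patients across hospitals, so that offset is counted as ordinary variation between patients. The test has no place for a hospital term.

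Air leak is where this matters most. The section on the choice of comparators justifies the Owner mask by less leakage through a better seal, so leak is the outcome closest to the device's rationale. It also has no meaningful value before a mask is on the face, whatever the general statement about before-and-after readings, so a change from baseline cannot cancel a device offset. A real difference in seal could go undetected for a reason that the analysis could remove.

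**Working it through.** **1. The plan's own figures.** The document gives no power figure for the ventilator outcomes. Its group sizes belong to the intubation rate and supply only the n used below. With n = [1.96·√(2p̄q̄) + 0.8416·√(p₁q₁ + p₂q₂)]² / δ²:

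- COVID-19, 30.2% against 10.2%: (1.96·√0.3224 + 0.8416·√0.3024)² / 0.04 = 62.1, so 63 per arm, as stated.
- Non-COVID, 61% against 41%: (1.96·√0.4998 + 0.8416·√0.4798)² / 0.04 = 96.9, so 97 per arm, as stated.

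**2. Inputs for the check.**

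- From the document: 63 and 97 per arm, three hospitals, blocks of 10, 1:1 allocation, two-sided 0.05.
- Assumed: hospitals of equal size, one ventilator type in each, normal readings with within-hospital SD 1, allocation blocked within hospital, and a share ρ of total variance due to hospital or ventilator.
- Mask effect: the size that gives 80% power on the normal approximation when ρ = 0. This is (1.96 + 0.8416)·√(2/63) = 0.50 SD, and 2.8016·√(2/97) = 0.40 SD.

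**3. Approximation.** With arms balanced within hospital, the hospital offsets cancel from the true sampling error of the mask difference. The pooled test still counts them, so its standard error is too large by 1/√(1−ρ). Hence

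power ≈ Φ(2.80 − 1.96/√(1−ρ)), and actual two-sided alpha ≈ 2Φ(−1.96/√(1−ρ)).

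| ρ | 1/√(1−ρ) | power | actual alpha |
|---|---|---|---|
| 0 | 1.000 | 80% | 5.0% |
| 0.1 | 1.054 | 77% | 3.9% |
| 0.3 | 1.195 | 68% | 1.9% |
| 0.5 | 1.414 | 51% | 0.6% |

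**4. Simulation with the rank tests themselves** (3,000 trials per setting; Monte Carlo standard error below 1 point):

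| ρ | 63 per arm, 0.50 SD: pooled / stratified power | 97 per arm, 0.40 SD: pooled / stratified power | Pooled test's actual alpha, 63 per arm |
|---|---|---|---|
| 0 | 77% / 77% | 78% / 77% | 4.3% |
| 0.1 | 74% / 76% | 75% / 77% | 4.4% |
| 0.3 | 64% / 77% | 63% / 77% | 1.9% |
| 0.5 | 45% / 78% | 46% / 77% | 0.6% |

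The stratified test is van Elteren's. Its alpha stays near 5% throughout. When hospital has no effect, the two tests have the same power within simulation error.

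**5. If there is one list rather than one per hospital.** The pooled test's alpha is then 4.4% to 5.2% across the settings run (ρ from 0 to 0.8), so it is not inflated. At 63 per arm its power is about 72%, 61% and 46% at ρ = 0.1, 0.3 and 0.5, against about 76% for the stratified test. The loss of power does not depend on how the implied per-hospital lists are read.

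**The case against.** **The variance share is unknown.** This stands. The SERVO-S is preferred, the document does not say how many hospitals lack one, and the share could be near zero. At 10% the loss is only 2 to 3 points. A reader might infer that ventilator differences will drown the mask difference. The document does not support that: power all but disappears only at shares well above 50% (about 4% at an assumed 80%).

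**The Mann-Whitney test is not the only analysis.** This stands in part. The GEE's covariates are not listed, and an analysis plan that is not shown may add hospital. But the between-group test for continuous outcomes is not left open. It is named twice, and in that form it cannot carry hospital. The point is the choice of test, not a missing detail.

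**Some of the ten readings have a baseline.** This stands for respiratory rate, which is measured before and after 1 h, and for FiO2, which the baseline PaO2/FiO2 requires. The argument is strongest for leak and weaker for these two.

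**Bias.** A reader might infer that an arm imbalance in one hospital would appear as a mask effect. Allocation is random, and step 5 shows no inflation of type I error even with a single list. The harm is lost power.

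**The setting is chosen to look bad.** This stands in part. The size of the leak effect is not given. With a 0.5 SD effect, pooled power at shares of 10%, 30% and 50% is about 90%, 84% and 68% at 97 per arm, and 99%, 97% and 93% if all patients are analysed together (160 per arm). With 0.8 SD at 63 per arm it is 99%, 98% and 92%. A large effect would survive pooling.

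**Hospital is only a proxy for device.** This stands. With several ventilator types inside one hospital, stratifying by hospital removes only part of the device variation.

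**Blood gases.** "Arterial blood gasses will be obtained according to the routines of each center participating in the research", so one might extend the point to them. They are not ventilator readings and have a baseline before NIV, so they are left out here.

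**Conclusion.** The point holds as one of efficiency for secondary outcomes. The named between-group test ignores the level at which the ventilator may vary and to which the allocation sequence is sent. At 63 per arm and 0.5 SD, the cost is nothing if hospital explains no variance, about 2 to 3 points of power at a 10% share, about 13 to 14 points at 30% and about 33 points at 50%. If arms are balanced within hospital, the pooled test is also conservative, with an actual alpha of about 1.9% at 30% and 0.6% at 50%. These figures rest on assumed shares, three equal hospitals, one ventilator type in each and normal readings. Intubation, the primary outcome, is not affected. Separately, the section that takes respiratory rate from the SERVO-S alone does not fit the section that permits another ventilator.

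**What to change.** - For the ventilator-read outcomes, replace the pooled Mann-Whitney test with a van Elteren test stratified by hospital, or compare the arms in the GEE with hospital as a fixed effect.
- Add the ventilator model to the case report form and show air leak by model as well as overall, because hospital removes device variation only where each hospital uses mainly one model. Start at once, since the model may be hard to recover after recruitment.
- Reconcile Vital signs and respiratory effort with Intervention description {11a} on the source of respiratory rate.

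The cost is one form field and a line or two of plan text. With three hospitals, the statistical downside is negligible: with no hospital effect, both tests have about 77% power at 63 per arm.

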### Outcomes {12}

#### Primary outcome measure

OTI rate in patients with or without suspicion or confirmation of SARS-CoV-2 infection submitted to NIV with Owner mask or conventional orofacial mask.

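### The secondary outcome NIV success has two definitions that do not agree and a 1 h deadline tied to neither; the physiological definition has oxygenation thresholds that patients can already meet at entry

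*Protocol article*

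**What the plan says.** Four places in the protocol article bear on this outcome.

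- **Abstract, Methods** lists among the secondary outcomes the "success rate of NIV (not progressing to OTI").
- **Intervention description {11a}**, in the text after Fig. 1, states "Success or reduction in the severity of RF will be considered by the oxygenation index" and gives the thresholds as "PaO_2_/FiO_2_ > 200, reduction in RR < 30 bpm and SpO_2_ ≥ 94" per cent.
- **Secondary outcome measure** lists "NIV success rate with masks [deadline: 1 h since the beginning of NIV"] and adds no definition.
- **Primary outcome measure** is the "OTI rate in patients with or without suspicion or confirmation of SARS-CoV-2 infection", compared between the two masks, with no time window in that statement.

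Two further statements matter for the physiological version. Eligibility criteria {10} admits patients "hospitalized with SpO_2_ ≤ 94% on room air or PaO_2_/FiO_2_ ≤ 300 mmHg", alongside a clinical indication for NIV. Intervention description {11a} has FiO2 set to reach an SpO2 of at least 94%, which is also the SpO2 threshold for success.

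**The concern.** A success rate will be read as evidence of efficacy, so the reader must know what was counted and when. Here the abstract and the body give different rules, and the outcome list gives a time point that belongs clearly to neither. Left like this, the definition could be settled after the data are seen, in a trial where only the data analyst is blinded.

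Each rule also has a weakness of its own. The intubation rule may carry no information beyond the primary outcome. The physiological rule sets absolute thresholds rather than a change from baseline, and the oxygenation thresholds overlap with the entry range. Patients who start above them and stay there count as successes whichever mask they wear, which pulls the two arms together.

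**Working it through.** The point is one of definition. No figure stated in the protocol depends on it, so the check compares the rules with each other and with the entry criteria.

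**1. Do the two rules classify patients alike?** Suppose RR and SpO2 satisfy the physiological rule in both patients below.

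| Patient | Physiological rule at 1 h | Intubation rule |
|---|---|---|
| PaO2/FiO2 210 at 1 h, intubated later | success (210 > 200) | failure |
| PaO2/FiO2 180 at 1 h, never intubated | failure (180 is not > 200) | success |

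They do not, and the disagreement runs in both directions.

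**2. What does the intubation rule add to the primary outcome?** Over the same window, success rate = 1 − OTI rate in each arm, so the between-arm difference only changes sign. Illustration with invented counts at the planned 63 per COVID arm: 19/63 against 6/63 intubated gives an uncorrected chi-squared of 8.433, p = 0.0037. The complement, 44/63 against 57/63 not intubated, gives the same 8.433 and the same p. If the 1 h deadline is applied instead, the outcome becomes freedom from intubation at 1 h, which no section describes.

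**3. Can the physiological rule be met at entry?**

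- *PaO2/FiO2.* Entry allows values up to 300 and success needs more than 200. Every patient above 200 and up to 300 enters with this component already met.
- *SpO2.* A patient who qualifies on room-air SpO2 (at most 94%) meets the threshold (at least 94%) only at exactly 94%. A patient who qualifies on PaO2/FiO2 while on oxygen can meet it freely. During NIV the threshold is also the FiO2 target, so this component partly records that the target was reached.
- *RR.* The eligibility section states no RR threshold. The wording of the success criterion has two readings.
  - Reading (a): RR below 30 at 1 h. A patient on oxygen with PaO2/FiO2 250, RR 26 and SpO2 96% satisfies the entry oxygenation line (250 ≤ 300) and all three success thresholds (250 > 200, 26 < 30, 96 ≥ 94) before the mask is fitted.
  - Reading (b): RR must fall. Nobody is a success at entry. But no size of fall is given, and oxygenation need not improve. A patient going from PaO2/FiO2 280 to 210 and RR 26 to 25, with SpO2 at least 94%, counts as a success although oxygenation worsened.

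**4. Form of the dilution.** Let q be the share of patients in each arm who meet the rule at baseline, and assume they all still meet it at 1 h in both arms. Let d be the true difference in success rate among the rest. The observed difference is then d × (1 − q). The multiplier is 0.70 at q = 30% and 0.50 at q = 50%. Both values of q are assumptions chosen to show the shape. The protocol gives no baseline distribution of PaO2/FiO2, RR or SpO2, and no expected success rate.

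**The case against.** Much can be said for the plan, and several stronger readings that a reader might infer are not supported.

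- **That this outcome simply repeats the primary.** This holds only for the intubation rule over the primary's window. With the 1 h deadline it is a different, if odd, outcome.
- **That patients are already successes when enrolled.** This needs reading (a) of the RR wording. The protocol's phrase includes the word reduction, and a required fall is a natural reading. Nor is it shown that entry as a whole has no RR limit: Recruitment {15} selects patients by a national society's NIV criteria, which are not reproduced. What stands is the overlap of the oxygenation thresholds.
- **That a 20-point effect shrinks to 14 or 10 points** (20 × 0.70 and 20 × 0.50). The 20 points are the assumed reduction in intubation in Sample size {14}, not an effect on success rate. The share q is unknown, and the formula assumes no baseline-positive patient deteriorates in either arm.
- **That baseline mix rather than the mask drives the rate.** This is not shown. Randomisation balances the mix in expectation, and chance imbalance can touch any outcome.

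It is also fair to say that PaO2/FiO2 improvement at 1 h and RR at 1 h are separate secondary outcomes, so the composite is not the only physiological evidence. Covariate adjustment may sit in an analysis plan that is not shown, and its absence here is not a fault. Finally, the thresholds in the intervention section might be meant as bedside criteria. The outcome list would then have only the abstract's rule, which fits poorly with a 1 h deadline, so the conflict would remain.

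**Conclusion.** The inconsistency stands on the text alone: two rules, one deadline, and no statement of which rule the deadline belongs to. The rules can give opposite answers for the same patient.

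The weakness of the physiological rule stands in a limited form. Patients can enter with the oxygenation components met. Depending on how the RR wording is read, either some can meet the whole composite at entry, or some can be counted as successes while oxygenation worsens. Any mask effect on the success rate would be diluted to the extent that patients who start above the thresholds stay there. The size cannot be computed from the documents.

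This is worth correcting before analysis because it decides what the success rate can show. It concerns one secondary outcome among many and leaves the primary outcome and the sample size untouched.

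**What to change.** 1. Reconcile the abstract, Intervention description {11a} and Secondary outcome measure to one definition of NIV success at 1 h, distinct from the primary outcome. State whether the RR component requires a fall or only a value below 30.
2. Analyse PaO2/FiO2 and RR at 1 h as continuous outcomes, adjusted for their baseline values.
3. Report the composite among patients who did not meet its thresholds at baseline. This subset is defined by values recorded before NIV, so the randomised comparison within it is preserved. Count intubation or death by 1 h as failure.

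The cost is mainly wording. Vital signs and respiratory effort already has RR and SpO2 taken before NIV and after 1 h, and the PaO2/FiO2 ratio section has the ratio before NIV and within 1 h. Because Arterial blood gas analysis gives a 1 to 12 h range, the text should say which sample supplies the 1 h value. The downsides are a smaller denominator for the composite, hence less precision for it, and slightly more analysis work. No treatment rule changes.
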